**FIGURE 1 dom16257-fig-0001:**
[figure not shown]
Stitching of data and linkage of datasets.^35^, ^36^

Following data linkage to the HES APC dataset, ICD codes for 17 cause‐specific mutually exclusive admission clusters (Appendix 1) will be extracted as identified in a recent epidemiological analysis for people with diabetes in England^11^: ischaemic heart disease, stroke, acute myocardial infarction (MI), diabetes‐related cancers, non‐diabetes related cancers, hyperglycaemic crisis, major amputations, minor amputations, skin and bone infections, respiratory infections, kidney infections, sepsis, respiratory disease (non‐infectious, non‐cancerous), renal disease, chronic kidney disease, liver disease.

More than 50% of deaths in the United Kingdom do not occur in hospital, with ONS mortality data considered the gold standard for mortality records.^33^ Following data linkage with the ONS national death registry, cause‐specific mortality across 12 mutually exclusive clusters (Appendix 2) will be extracted as identified in a recent epidemiological study identifying causes of death in patients with diabetes in England^34^: ischaemic heart disease, stroke, other circulatory, other cancer, diabetes‐related cancer, dementia, diabetes, liver, renal, respiratory, other, injuries. In line with current reconciling guidelines date of death and cause of death will be taken from CPRD to enable linkage for the 25.11% of patients in England that are ineligible for linkage with ONS.^33^

The following recommendations will be applied when linking data from CPRD to ONS mortality data.^33^
If only CPRD date of death is present, this can be used as a reliable piece of information and has been previously validated.If only ONS mortality information is present, its date and causes of death can be used if the linkage rank is ≤2 (Table 2) and the date of death is within the linkage period being examined.If both CPRD and ONS dates of death are available, ONS will be used for the date of death and cause of death when the match rank is ≤2 and the date of death is within the linkage period being examined.If both CPRD and ONS are present and ONS date of death is outside the linkage period, or the match is ≥3 the CPRD date will be used to validate ONS. If the dates coincide ONS date of death and cause of death can be used. If not only CPRD date will be used.

**TABLE 2 dom16257-tbl-0002:** National Health Service (NHS) digital 8‐step linkage algorithm.^33^

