## APPENDIX A

**TABLE A1 dom16257-tbl-0003:** ICD‐10 codes for each underlying cause of hospitalisation and cause groupings [1].

Underlying causes	ICD‐10 Codes	Tier 1 cause groupings	Tier 2 Cause groupings
Malignant neoplasm of liver and intrahepatic bile ducts	C22	Cancers	DM‐related cancers
Malignant neoplasm of colon, rectosigmoid junction and rectum (i.e. colorectal)	C18, C19, C20	Cancers	DM‐related cancers
Malignant neoplasms of digestive organs except liver and intrahepatic bile ducts or colorectal	C15–C17, C21, C24, C26	Cancers	All other cancers
Malignant neoplasm of gallbladder	C23	Cancers	DM‐related cancers
Malignant neoplasm of pancreas	C25	Cancers	DM‐related cancers
Malignant neoplasms of lymphoid, haematopoietic and related tissue	C81–C96	Cancers	All other cancers
Malignant neoplasm of trachea, bronchus and lung	C33–C34	Cancers	All other cancers
Malignant neoplasm of prostate	C61	Cancers	All other cancers
Malignant neoplasm of breast	C50	Cancers	DM‐related cancers
Malignant neoplasm of cervix	C53	Cancers	All other cancers
Malignant neoplasm of corpus uteri	C54	Cancers	DM‐related cancers
All other neoplasms	C00–C14, C27–C32, C35–C49, C51–C52, C55–C60, C62–C80, C97–D48	Cancers	All other cancers
Respiratory	J00–J98, J19, J22–J99	Respiratory, renal & liver	Respiratory
Respiratory infection	J12–J18, J09–J12, J20–21, A15–A19	Infections	Respiratory infection
Diabetes	E10–E14, excluding E10.0, E10.1, E11.0, E11.1, E12.0, E12.1, E13.0, E13.1, E14.0, E14.1	Diabetes	Diabetes
Acute Myocardial Infarction	I21–I22	Vascular	Acute myocardial infarction
Other ischaemic heart disease & heart failure	I20, I23–I25, I50	Vascular	Ischaemic heart disease
Stroke (cerebrovascular)	I60–I69	Vascular	Stroke
Major Lower limb amputations	OPCS codes: 093–095, 098–099	Amputations	Major amputations
Minor lower limb Amputations	OPCS codes: 101, 104, 108–109, 111–112, 118–119	Amputations	Minor amputations
Hyperglycaemic crisis	E10.0, E10.1, E11.0, E11.1, E12.0, E12.1, E13.0, E13.1, E14.0, E14.1	Diabetes	Hyperglycaemic crisis
Renal disease	N00–N09, N12–N14, N17, N19–N28	Respiratory, renal & liver	Renal disease
ESRD	N18	Respiratory, renal & liver	Renal disease
Kidney infection	N10–11, N15–N16, N30, N39	Infections	Kidney infection
Liver disease	K70–77	Respiratory, renal & liver	Liver disease
Skin, soft tissue and bone infections	L03, L97, I96, M86, B35–49	Amputations	Skin and bone infections
Sepsis	A40–A41	Sepsis	Sepsis

^1^

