Pearson‐Stuttard J, Cheng YJ, Bennett J, *et al*. Trends in leading causes of hospitalisation of adults with diabetes in England from 2003 to 2018: an epidemiological analysis of linked primary care records. *Lancet Diabetes Endocrinol*. 2022;10. DOI: 10.1016/S2213‐8587(21)00288‐6.

**TABLE A2 dom16257-tbl-0004:** ICD‐10 codes for each underlying cause of mortality and cause groupings [1].

Underlying causes	ICD‐10 Codes	Tier 1 cause groupings	Tier 2 Cause groupings
Malignant neoplasm of liver and intrahepatic bile ducts	C22	Cancers	DM‐related cancers
Malignant neoplasm of colon, rectosigmoid junction and rectum (i.e. colorectal)	C18, C19, C20	Cancers	DM‐related cancers
Malignant neoplasms of digestive organs except liver and intrahepatic bile ducts or colorectal	C15–C17, C21, C24, C26	Cancers	All other cancers
Malignant neoplasm of gallbladder	C23	Cancers	DM‐related cancers
Malignant neoplasm of pancreas	C25	Cancers	DM‐related cancers
Malignant neoplasms of lymphoid, haematopoietic and related tissue	C81–C96	Cancers	All other cancers
Malignant neoplasm of trachea, bronchus and lung	C33–C34	Cancers	All other cancers
Malignant neoplasm of prostate	C61	Cancers	All other cancers
Malignant neoplasm of breast	C50	Cancers	DM‐related cancers
Malignant neoplasm of cervix	C53	Cancers	All other cancers
Malignant neoplasm of corpus uteri	C54	Cancers	DM‐related cancers
All other neoplasms	C00–C14, C27–C32, C35–C49, C51–C52, C55–C60, C62–C80, C97–D48	Cancers	All other cancers
Respiratory	J00–J99	Other	Respiratory
Diabetes	E10–E14	Other	Diabetes
Ischaemic Heart Disease	I20–I25	Vascular	Ischaemic heart disease
Stroke (cerebrovascular)	I60–I69	Vascular	Stroke
Other circulatory	I00–I19, I26–I59, I70–I99	Vascular	Other circulatory
Renal disease	N00–N28	Other	Renal disease
Liver disease	K70–77	Other	Liver disease
Intentional injury – assault	X85–Y09, Y871	Other	Accidents
Intentional Injury – self harm	X60–X84, Y870	Other	Accidents
Intentional Injury – other intentional injury	Y35, Y36	Other	Accidents
Unintentional injury	V01–X59, Y40–Y86, Y88, Y89	Other	Accidents
Dementia and Alzheimer's	F00–F03, G30	Other	Dementia
All other ICD codes		Other	Other

^1^
Pearson‐Stuttard J, Bennett J, Cheng YJ, *et al*. Trends in predominant causes of death in individuals with and without diabetes in England from 2001 to 2018: an epidemiological analysis of linked primary care records. *Lancet Diabetes Endocrinol*. 2021;9. DOI: 10.1016/S2213‐8587(20)30431‐9.

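### The admission cluster named ischaemic heart disease includes heart failure while the mortality cluster of that name excludes it, and the residual cancer cluster takes in non-malignant D codes

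*Protocol article*

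**What the plan says.** Section 3.4 (Data processing and analysis) plans "17 cause‐specific mutually exclusive admission clusters" from the hospital data, and a separate set of mortality clusters from the death registry. *Ischaemic heart disease* appears by name in both lists. Heart failure is named in neither. The admission list is said to be used "as identified in a recent epidemiological analysis for people with diabetes in England", and the mortality list is credited to a second published study.

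The code lists are in Appendix A:

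- **Table A1 (admissions).** The row "Other ischaemic heart disease & heart failure" has codes "I20, I23–I25, I50", Tier 1 *Vascular* and Tier 2 *Ischaemic heart disease*. Acute myocardial infarction (I21–I22) is its own Tier 2 cluster.
- **Table A2 (deaths).** *Ischaemic heart disease* is I20–I25. *Other circulatory* is "I00–I19, I26–I59, I70–I99".
- **Both tables.** The row *All other neoplasms* has codes "C00–C14, C27–C32, C35–C49, C51–C52, C55–C60, C62–C80, C97–D48", with Tier 1 *Cancers* and Tier 2 *All other cancers*.
- **Table A1 only.** The row "Skin, soft tissue and bone infections" has Tier 1 *Amputations*, while the kidney and respiratory infection rows have Tier 1 *Infections*.

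**The concern.** Objectives 2 and 3 examine cause-specific admissions and cause-specific mortality for the same exposure. A cause-specific estimate is only as informative as the match between its label and its codes.

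Two labels do not match. An association with heart failure admissions would appear in the results as an association with ischaemic heart disease, and the list of outcomes in Section 3.4 would not tell the reader that heart failure is inside. The mortality result under the same name would refer to a different set of conditions. In addition, the cluster that Section 3.4 presents as non-diabetes-related cancer would count admissions for neoplasms that are not malignant.

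**Working it through.** The plan gives no figure to reproduce here, so the check is a comparison of code sets followed by an illustration on assumed shares.

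**Step 1. Which level is analysed.** The admission outcomes named in Section 3.4 follow the Tier 2 column of Table A1, not the broader Tier 1 column. For example, they separate acute MI, ischaemic heart disease and stroke, which share one Tier 1 group. A Tier 2 mislabel therefore reaches a named outcome, and a Tier 1 mislabel does not.

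**Step 2. Ischaemic heart disease, code by code.**

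| Code | Table A1, Tier 2 (admissions) | Table A2, Tier 2 (deaths) |
|---|---|---|
| I20, I23–I25 | Ischaemic heart disease | Ischaemic heart disease |
| I21–I22 | Acute myocardial infarction | Ischaemic heart disease |
| I50 | Ischaemic heart disease | Other circulatory (within I26–I59) |

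The I21–I22 difference follows from making acute MI a separate admission cluster. The I50 difference has no such explanation: the same code is ischaemic in one table and not in the other. The union of I20, I23–I25 with I21–I22 is exactly I20–I25, so an admission set that matches Table A2 can be built once I50 is taken out.

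**Step 3. The residual cancer row.** Table A1 has 12 neoplasm rows. Eleven are labelled as malignant neoplasms. The twelfth, the catch-all, drops that word and extends through D48. D00–D48 spans 49 three-character positions (48 − 0 + 1). In ICD-10, the classification the protocol adopts, this block holds in situ, benign and uncertain neoplasms. Both tiers nevertheless call the row cancer. Table A2 repeats the same range and assignment.

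**Step 4. What mixing does to an estimate.** Let s be the share of the cluster's admissions in the never group that belong to the added condition. The rate ratio for the whole cluster is then

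RR(cluster) = (1 − s) × RR(named disease) + s × RR(added condition).

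The documents give neither s nor the rate ratios. All are assumed.

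- *Effect on heart failure only (1.00 on ischaemic disease, 0.80 on heart failure).*
  - s = 0.1: 0.90 + 0.08 = 0.98
  - s = 0.3: 0.70 + 0.24 = 0.94
  - s = 0.5: 0.50 + 0.40 = 0.90
  - s = 0.6: 0.40 + 0.48 = 0.88
- *Effect on the named disease only (0.90), none on the added condition (1.00).*
  - s = 0.1: 0.81 + 0.10 = 0.91
  - s = 0.3: 0.63 + 0.30 = 0.93
  - s = 0.5: 0.45 + 0.50 = 0.95

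The first case shows an apparent ischaemic effect that comes wholly from heart failure. The second shows a real effect pulled towards 1, and the same arithmetic applies to malignant disease diluted by D codes. The formula is exact for event rates and only a guide for first-event hazard ratios.

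**Step 5. The amputation label.** Section 3.4 lists "major amputations, minor amputations, skin and bone infections, respiratory infections" as separate clusters, and Table A1 gives the skin and bone row its own Tier 2 label. The Tier 1 heading therefore changes no outcome named in the text.

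**The case against.** The best defence has four parts.

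1. *The pooling is disclosed.* The Table A1 row says openly that it combines other ischaemic disease with heart failure, and four of its five categories are ischaemic. This stands as far as it goes: the fault is a mislabelled composite. But the disclosure is only in an appendix row label. The Tier 2 name and the main text both drop heart failure.

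2. *The groupings come from two published analyses, one of admissions and one of deaths, and following them keeps results comparable with those sources.* This is a fair reason to retain the source grouping somewhere. It does not remove the conflict, because this protocol brings both groupings into one study under one name. The sources are not at hand, so fidelity to them cannot be checked.

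3. *No side-by-side comparison of the two ischaemic results is planned.* That is correct. The mislabelling still affects the admission result on its own, and one exposure studied for both outcomes invites the comparison.

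4. *The D codes sit in a residual row labelled neoplasms.* That is also correct, and the row keeps all its malignant codes. The effect is dilution of a catch-all, with no volume to size it.

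A reader might go further and infer that cause-specific effects would be reported for the wrong disease, or that a change in cellulitis would be published as a change in amputations. The documents support neither. The first overstates a mixed cluster and a diluted one. The second would need a Tier 1 *Amputations* analysis, and the protocol describes none. Nor is leaving acute MI out of the admission cluster a fault, since mutually exclusive clusters require it once MI stands alone.

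**Conclusion.** The point holds for two clusters. The admission outcome called ischaemic heart disease contains heart failure, and Table A2 contradicts that use of the name. *All other cancers* contains D00–D48 in both tables. The heart failure part rests only on the two code lists and the outcome names in Section 3.4. The D-code part also uses the ICD-10 meaning of the D block.

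The size is unknown. The range of 0.98 to 0.88 rests on assumed heart failure shares of 10% to 60% and assumed rate ratios. It shows direction and form, and is not an estimate for this cohort. For deaths, no particular harm from the D codes is shown beyond the mislabel.

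The reach is limited. All-cause admissions and mortality, which carry the stated hypotheses, are unaffected, as are the MI and stroke components of 3P-MACE. The Tier 1 heading over skin, soft tissue and bone infections is inconsistent with the kidney and respiratory infection rows, but it is only a tidy-up. The change should be made before extraction, but it does not threaten the main analysis.

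**What to change.** Before the data are extracted:

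1. In Table A1 and the Section 3.4 list, make I50 a separate *heart failure* admission cluster and leave I20 and I23–I25 as *other ischaemic heart disease*. At minimum, rename the present cluster in both places so that heart failure is in the name.
2. Wherever the admission result is shown beside the Table A2 mortality cluster, report I20–I25 combined, that is, *other ischaemic heart disease* plus *acute myocardial infarction*.
3. In both tables, restrict *All other cancers* to the malignant C codes and move D00–D48 to a named row for in situ, benign and uncertain neoplasms.
4. As a tidy-up, change the Tier 1 entry of the skin, soft tissue and bone infection row to *Infections*.

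The cost is an edit to the code lists, one extra admission cluster, one extra neoplasm row in each table, and a revised cluster count in the text. The altered groupings would no longer match the published sources. Keeping the source version as a supplementary table preserves that comparison.
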